## Abstract

Diabetic peripheral neuropathy (DPN) is the leading cause of disturbances in reactive balance control. The repeated, external mechanical perturbations in perturbation-based balance training(PBBT) evoke balance recovery strategies; which subsequently improve reactive balance performance. Using the practice schedule concept of motor learning in the design of PBBT is a relatively new approach related to balance exercises. This study aims to investigate the effects of blocked and random PBBT on reactive balance control and its persistency and transfer to conditions different from those experienced during training.

Individuals with DPN will be recruited and randomly allocated to one of the three groups: random, blocked, and control group. Random and blocked PBBT groups will receive single-session balance training, including unexpected perturbations of platform during quiet standing in two directions (anterior and posterior), and three difficulty levels of platform motion (displacement, velocity, and acceleration). Each balance perturbation in blocked group will be repeated over blocks of four trials. For the random group, perturbation sequence will be unpredictable for these four trials in each block. Primary outcomes (i.e., center of pressure variables, reaction time, movement time, and total response time variables) will be assessed at baseline as well as immediately and one day after intervention.

Specifications table

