**Table utbl0001:** 

Subject area	Neuroscience
**More specific subject area**	Learning
**Name of your protocol**	Random vs. Blocked Perturbation Training on Reactive Balance Control in Peripheral Neuropathy: Protocol Study for a Randomized Controlled Trial
**Reagents/tools**	- Participants' demographic information - Neuropathy Disability Score to assess the severity of neuropathy - Mini-Mental State Examination to test cognitive functioning - Short Beck Depression Inventory to assess depression in adolescents and adults -The Computerized Dynamic Posturography system [Smart EquiTest CRS (NeuroCom International Inc.Clockamas, Oregon)] to measure balance and postural control - long single force plate (EquiTest CRSVR NeuroComVR International, Clackamas, OR) and the screen to assess speed and coordination - Mini-balance evaluation systems test to evaluate dynamic balance
**Experimental design**	This is a protocol study for a single-blind randomized controlled trial. Individuals with DPN will be recruited and randomly allocated to one of the random, blocked, and control groups. Random and blocked PBBT groups will receive single-session PBBT involving platform perturbations during quiet standing in the anterior and posterior directions at three levels of difficulty. The control group will receive no intervention. All patients will be assessed at three time points (baseline, end of the session, and 24 hours later). Primary outcomes include center of pressure variables, reaction time, movement time, and total response time.
**Trial registration**	IRCT20240111060675N1
**Ethics**	- All individuals will provide written informed consent. - This study will be performed in line with the principles of the Declaration of Helsinki. Approval was granted by the Ethics Committee of Ahvaz Jundishapur University of Medical Science (approval date 2024-01-06/ number IR.AJUMS.REC.1402.537).
**Value of the Protocol**	- This study is the first to examine the effectiveness of PBBT using a blocked and random practice sequence on the acquisition, retention, and generalizability of reactive balance skills in individuals with DPN. - PBBT leads to faster balance adaptation and may potentially achieve better results with fewer sessions compared to traditional methods. - The results of this study will be helpful for the development of therapeutic exercises aimed at improving balance control and reducing the risk of falling in real-life challenges.

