### Methods of measurement

Participants will be evaluated at a pre-test (T1), post-test (T2), and retention test (T3) using the same protocol. In these tests, each participant will receive two trials of perturbations with each of the three difficulty levels and the anterior direction with a serial sequence (totaling six trials). Serial sequence refers to the sequence or arrangement of different skills, or variations of a skill, in a specific order, one after another in a predictable manner. The post-test is applied five minutes after PBBT.

The retention test will be applied at the beginning of the second session. After a five-minute rest, patients will be tested in three different transfer tasks.

Transfer tasks will be assessed as follows:

Cognitive dual-tasking: counting backward by three from a random number selected between 100 and 200 by the outcome assessor during perturbations. Participants will be asked to maintain balance while they attempt to perform the consecutive mental subtractions task as quickly and as accurately as possible, speaking aloud the result. During this cognitive transfer task, the high level of difficulty perturbation will be applied in the anterior direction, with two trials.

Different mode of perturbation: In this test, the perturbation will be in the anterior (dorsiflexion) direction with a rotational mode, with two trials.

Choice Stepping Reaction Time (CSRT) Test: for assessing the transferability of improvements obtained in the reactive balance responses to the balance responses against internal perturbations, the CSRT test will be used. In this test, patients will stand on a long force plate of the Neurocom device with their feet hip-width apart, and while looking at the screen in front of them, colored boxes are randomly displayed on the right or left side of the screen. Participants will be instructed to step as fast as possible with the respective leg and then return to the starting position. Each participant will perform 10 trials, which include five repetitions for each direction randomly [19]. A one-minute rest period will be allowed between transfer tests. In order to have a baseline in this study, all transfer tests will be assessed before training.

Reactive balance control is the main outcome in this study, which will be recorded with the Computerized Dynamic Posturography system in the standing position [20].

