Reactive response variables will be collected by the Smart EquiTest CRS (NeuroCom International Inc.Clockamas, Oregon) device, including: (1) peak center of pressure (CoP) displacement in anterior and posterior directions which indicates the maximum distance that the location of the CoP reaches in the anterior or posterior direction relative to the baseline [21]; (2) response time, defined as the time interval between the start of platform movement (as a stimulus) and the initiation of the participant's active response; (3) peak values of CoP velocity in the anterior and posterior directions following the onset of platform motion.

CSRT test is used to measure how quickly and accurately a person can step in response to a visual stimulus [22]. The equipment will be used consisted of the long single force plate (EquiTest CRSVR NeuroComVR International, Clackamas, OR) and the screen in front of patients.

In the step execution data, the following temporal variables will be examined: (1) Reaction time (RT) defined as the time interval between the appearance of the stimulus and the movement initiation (lifting the corresponding leg); (2) Movement time (MVT) defined as the time interval between the start of the movement and the foot strike; and (3) Total response time (TRT) calculated as the sum of RT and MVT [23].

In addition to other interventions, the Mini-Balance Evaluation Systems Test (Mini-BESTest) will be performed as a clinical assessment tool. This test evaluates dynamic balance, particularly in individuals with balance impairments [24].

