### Statistics

All data will be analyzed using SPSS version 28. Baseline data and demographic characteristics will be described using descriptive statistics.

Data distribution normality will be confirmed using the Kolmogorov–Smirnov test. The main effects and interactions of group (blocked sequence, random sequence, and control), time (pre-test and post-test), and difficulty level (low, medium and high) on CoP variables will be compared using three-way repeated measures ANOVA. In addition, the main effects and interactions of groups, time (post-test and retention), and difficulty level (low, medium, and high) on CoP variables will be compared using three-way repeated measures ANOVA. Also, a one-Way ANOVA will be used to compare the means of CoP variables between the retention and transfer phases across three groups. Moreover, a two-way repeated measure ANOVA will be used to determine the main effects and interactions of group and time (pre-test, post-test, and transfer) on RT, MVT, and TRT variables of the CSRT test. A post-hoc Bonferroni test will be used for multiple comparisons.

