### Sample size calculation

Due to a lack of similar studies, we conducted a pilot study on 30 individuals with diabetic neuropathy (10 for each group). Sample size was calculated in G*power software version 1.9.4.3 and was based on the primary outcome of the pilot study, the difference between means of the peak CoP velocity in the anterior direction measured with the computerized dynamic posturography at T1 and T2. Based on the statistical power of 80% and the probability of the first type error of 0.05, the sample size was estimated to be about 20 individuals in each group.

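### Several outcomes are called primary without ranking, the sample size rests on one of them, and no stated adjustment spans outcomes or phases

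*Protocol article*

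**What the plan says.** Four places in the Protocol article bear on which outcome is primary.

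- **Abstract:** "Primary outcomes (i.e., center of pressure variables, reaction time, movement time, and total response time variables". No order is given.
- **Specifications table, experimental design row:** "Primary outcomes include center of pressure variables, reaction time, movement time, and total response time". The same families, again unranked.
- **Methods of measurement:** "Reactive balance control is the main outcome in this study", recorded by posturography in standing. The Choice Stepping Reaction Time (CSRT) test, which yields reaction time (RT), movement time (MVT) and total response time (TRT), appears there as one of three transfer tasks.
- **Sample size calculation:** the basis is "the difference between means of the peak CoP velocity in the anterior direction measured with the computerized dynamic posturography at T1 and T2", described as the primary outcome of the pilot study.

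The platform variables listed under Methods of measurement are "peak center of pressure (CoP) displacement in anterior and posterior directions", "peak values of CoP velocity in the anterior and posterior directions following the onset of platform motion", and "response time, defined as the time interval between the start of platform movement (as a stimulus) and the initiation of the participant's active response". TRT is defined as RT plus MVT.

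The Statistics section plans, for the CoP variables, one three-way repeated measures ANOVA for acquisition (pre-test and post-test), a second for retention (post-test and retention test), and a one-way ANOVA for transfer. RT, MVT and TRT get a two-way repeated measures ANOVA over pre-test, post-test and transfer. The only multiplicity statement is "A post-hoc Bonferroni test will be used for multiple comparisons". A type I error of 0.05 appears only in the sample size section.

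**The concern.** The article describes its primary outcome at three levels: a set of variables, a construct, and one variable over one time window. It gives no rule joining them. CSRT times are primary in two places and a transfer measure in a third. Platform response time is a reactive response variable, but it is unclear whether it belongs to the primary CoP variables.

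This matters more than usual here. The Background expects blocked practice to help acquisition, and random practice perhaps to acquire more slowly but to retain and transfer better. On the trial's own theory, the favoured schedule can change with the phase. With several unranked primary variables and three phases open, a claim for either schedule could be selected after the data are seen, and the stated power would apply to only one of the possible claims.

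**Working it through.** **1. The plan's own figure.** About 20 per group, 60 in total, at 80% power and alpha 0.05. This cannot be reproduced, because the article gives no effect size, SD, correlation or test. Solving backwards under an assumed one-way three-group ANOVA, 20 per group has 80% power at f = 0.41. This serves only as a reference point for step 5.

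**2. Count of primary outcomes.** The article gives no count. From Methods of measurement:
- CoP displacement, anterior and posterior: 2
- CoP velocity, anterior and posterior: 2
- RT, MVT, TRT: 3
- Total 2 + 2 + 3 = 7, or 8 if platform response time counts as primary.

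**3. Family-wise error over the outcomes.** Two assumptions are needed: each outcome is tested at 0.05, and one significant result is enough. For m independent tests the error is 1 − 0.95^m. For correlated tests the figures come from equicorrelated two-sided z tests.

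| Pairwise correlation (assumed) | 7 outcomes | 8 outcomes |
|---|---|---|
| 0 | 1 − 0.95^7 = 30% | 1 − 0.95^8 = 34% |
| 0.3 | 27% | 30% |
| 0.5 | 23% | 25% |
| 0.7 | 18% | 19% |
| 0.9 | 11% | 12% |

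The outcomes are certainly correlated, since TRT is an exact sum of two others, so the top row is an upper-end illustration.

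**4. Family-wise error over the planned ANOVAs.** Take one group test per ANOVA. The 4 CoP variables pass through 3 phases and the 3 CSRT variables have one ANOVA each: 4 × 3 + 3 = 15 tests. If independent, 1 − 0.95^15 = 54%. At correlation 0.3, 0.5 and 0.7 this falls to 46%, 36% and 26%. With platform response time as a fifth platform variable, 5 × 3 + 3 = 18 tests and 1 − 0.95^18 = 60%.

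**5. Cost of adjusting over all outcomes.** Bonferroni over seven gives 0.05/7 = 0.0071. At f = 0.41, power with 20 per group falls from 80% to about 53%, and 80% power would need about 31 per group (93 in total). Over eight, 0.05/8 = 0.00625, power is about 51%, and about 32 per group (96 in total) are needed. Naming a single primary outcome avoids this cost.

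**The case against.** The strongest reply is that this is a condensed article. A multiplicity rule usually sits in the statistical analysis plan or full protocol, which is not shown, so its absence here proves nothing. That stands for the rule. It does not cover the description of the primary outcome, which the article states more than once and not consistently.

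Several stronger readings are tempting, and the documents do not support them.

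- *The sample size uses a different primary outcome.* It does not: anterior peak CoP velocity is one of the CoP variables in the primary set, and reactive balance control is the construct those variables measure. The mismatch is between a set and one of its members.
- *The trial has no primary result.* The sample size section does point to one variable and one window, although it attributes that status to the pilot study.
- *The outcomes are co-primary and therefore inflate the error.* Co-primary in the strict sense means that all must succeed, which does not raise the type I error. Inflation needs a rule that any one success suffices, and the article states neither rule.
- *Every primary outcome is tested in all three phases.* Only the CoP variables are. RT, MVT and TRT have one ANOVA each.
- *A false positive is near certain.* Counting every group term gives 2 × 4 × 4 = 32 for the three-way ANOVAs, 4 × 2 = 8 for two transfer tasks and 3 × 2 = 6 for the CSRT, so 46 tests and 1 − 0.95^46 = 91%. That count treats the tests as independent although both three-way ANOVAs use the same post-test data. It also includes group main effects and group-by-difficulty terms that average over pre-test data and so do not test a treatment effect, and it presumes a separate transfer ANOVA per task, which the Statistics section does not say.

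**Conclusion.** The concern holds in a limited form. What is firm, and needs no assumption, is that the Abstract, specifications table, Methods of measurement and Sample size calculation do not identify one primary outcome and time point consistently, and that the stated 80% power belongs to one variable over one window.

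The error-rate figures are conditional. If any single success counts and each test is run at 0.05, the family-wise error over seven outcomes lies between about 11% (correlation 0.9) and 30% (independence), and reaches at most 54% over the 15 group tests. All of these exceed 5%. The seven-outcome figures alone do not show that a false positive is more likely than not. As worded, the post-hoc Bonferroni reads as protecting pairwise group comparisons within an ANOVA, and nothing in the article extends it to outcomes or phases.

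**What to change.** Before outcome data are analysed:

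1. Name one primary variable, one time point and one group comparison. Anterior peak CoP velocity, T1 to T2, fits the existing sample-size basis and keeps alpha at 0.05 and about 20 per group. The sample size section does not say which group contrast it powers. If a single pair is chosen, such as random versus blocked, check that the stated n supports it.
2. State how the three difficulty levels enter the primary analysis.
3. Make the other CoP, response-time and CSRT variables, and the retention and transfer phases, secondary (for example Holm-adjusted) or explicitly exploratory. Say whether platform response time is among them.
4. Do not make the retention test depend on a significant random-versus-blocked result at T2. The Background expects random practice to acquire more slowly but retain better, so such a gate could block the test the theory favours. If the sponsor regards retention at T3 as the main hypothesis, it should be named as primary and the sample-size basis rechecked.
5. Bring the Abstract, specifications table, Methods of measurement and Sample size calculation into agreement.

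The cost is a wording amendment, and some outcomes lose primary status. The Protocol validation section reports that outcome assessment had not begun, so the change could still be made without knowledge of results. After analysis it would not be credible.

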**Table utbl0001:** 

Subject area	Neuroscience
**More specific subject area**	Learning
**Name of your protocol**	Random vs. Blocked Perturbation Training on Reactive Balance Control in Peripheral Neuropathy: Protocol Study for a Randomized Controlled Trial
**Reagents/tools**	- Participants' demographic information - Neuropathy Disability Score to assess the severity of neuropathy - Mini-Mental State Examination to test cognitive functioning - Short Beck Depression Inventory to assess depression in adolescents and adults -The Computerized Dynamic Posturography system [Smart EquiTest CRS (NeuroCom International Inc.Clockamas, Oregon)] to measure balance and postural control - long single force plate (EquiTest CRSVR NeuroComVR International, Clackamas, OR) and the screen to assess speed and coordination - Mini-balance evaluation systems test to evaluate dynamic balance
**Experimental design**	This is a protocol study for a single-blind randomized controlled trial. Individuals with DPN will be recruited and randomly allocated to one of the random, blocked, and control groups. Random and blocked PBBT groups will receive single-session PBBT involving platform perturbations during quiet standing in the anterior and posterior directions at three levels of difficulty. The control group will receive no intervention. All patients will be assessed at three time points (baseline, end of the session, and 24 hours later). Primary outcomes include center of pressure variables, reaction time, movement time, and total response time.
**Trial registration**	IRCT20240111060675N1
**Ethics**	- All individuals will provide written informed consent. - This study will be performed in line with the principles of the Declaration of Helsinki. Approval was granted by the Ethics Committee of Ahvaz Jundishapur University of Medical Science (approval date 2024-01-06/ number IR.AJUMS.REC.1402.537).
**Value of the Protocol**	- This study is the first to examine the effectiveness of PBBT using a blocked and random practice sequence on the acquisition, retention, and generalizability of reactive balance skills in individuals with DPN. - PBBT leads to faster balance adaptation and may potentially achieve better results with fewer sessions compared to traditional methods. - The results of this study will be helpful for the development of therapeutic exercises aimed at improving balance control and reducing the risk of falling in real-life challenges.

## Background

Diabetic peripheral neuropathy (DPN) affects over 50% of patients with type2 diabetes [1]. In these individuals, the degeneration of afferent and efferent nerve axons can lead to sensory loss, delayed reaction time, and muscle weakness, resulting in balance dysfunction and higher fall risk [2,3]. In daily life, falls mostly occur during dynamic activities due to an inability to control balance in response to mechanical perturbations caused by internal and external forces (impaired reactive balance control) [4]. Reactive balance control is one of the most important postural control strategies for preventing falls when the balance system is perturbed [5]. In individuals with DPN, damage to nerve fibers causes sensory impairment that slows the processing of sensory information and subsequent motor responses leading to a slower and less effective reactive balance response [6].

Research suggests that strategies to recover from unexpected loss of balance differ from voluntary exercises, indicating that fall prevention training should incorporate unexpected perturbations to increase the effectiveness of exercise [7]. Perturbation-based balance training (PBBT) is a form of reactive balance training that exposes individuals to repeated, external mechanical perturbations in a safe and controlled environment to elicit postural control reactions [8]. In the only study performed in individuals with DPN, a single PBBT session improved reactive balance, but the optimal sequence of perturbations for effective motor learning remains unknown [3].

Using the practice schedule concept of motor learning to PBBT is a relatively new approach [8]. There are two types of practice schedules:constant and variable. Constant practice involves repeatedly practicing a single skill. In contrast, variable practice exposes the learner to a variety of related skills [9]. Performing variable skills within a single practice session creates contextual interference (CI), a phenomenon that enhances long-term learning by requiring frequent shifts between task variations [10]. Variable practice is broadly categorized into blocked or random schedules [11]. Blocked practice, associated with low CI, involves repeated performing of one task before moving to another, facilitating skill acquisition and performance during training [11]. Random practice, associated with high CI, refers to practice task variations in the same session in a pseudo-random order [11]. Although acquisition may be slower, random practice leads to better skill retention and transfer to new situations [12].

Given the crucial role of reactive responses in preventing falls, which are often sudden and occur in any direction [13], it is important to investigate how different practice schedules affect the ability of individuals with DPN to react to balance perturbations. In addition, In individuals with DPN, compensating for sensory loss increases cognitive demand, causing balance impairments during dual-tasking [6]. Since reactive balance requires attention, dual tasks may further disrupt postural control strategies in these individuals [14]. Therefore, assessing the generalizability of improvements in reactive balance control during single-task to dual-tasks may be useful for enhancing dual-task interference on reactive balance performance in individuals with DPN.

To the best of our knowledge, no study has yet investigated the effects of different practice schedules of PBBT on reactive balance control in individuals with DPN. Therefore, this study aims to compare the effects of blocked and random practice of PBBT on the acquisition, retention, and generalizability of acquired reactive balance skills in individuals with DPN. Our findings would be helpful for the development of preventive and therapeutic strategies to reduce the risk of falls and improve reactive balance control in individuals with DPN.

